## 8.2 Screening and Eligibility Assessment

Once participants have given consent, they will complete two screening questionnaires (PCL-5 and PHQ-9) to assess eligibility. Participants who score in the clinical range on measures of post-traumatic stress and depression will be contacted by the trained research assistant. If their symptoms are interfering with their life and they would like treatment, the research assistant will offer them information on how to access evidence-based treatment for these conditions in local services. They will be excluded from the trial.

Eligible participants who wish to participate and have given consent will be emailed a link to complete their initial baseline questionnaires and an appointment will be made to collect a plasma sample and give them their saliva collection tubes.

## 8.3 Informed Consent

After receiving detailed written and verbal information about the exact nature of the trial and what it will involve for them, and if agreeing to participate in the trial, the participant will electronically sign their name on the latest approved version of the consent form. They will complete the two screening questionnaires (PCL-5 and PHQ-9) and if eligible, they will personally sign the consent form when they meet the research assistant at their face-to-face appointment for the plasma sample, which will be scheduled within one week of signing the electronic consent form.

The information sheet and consent form state the participant is free to withdraw from the trial at any time for any reason without penalty, by advising the researchers of this decision.

The participant will be allowed as much time as wished to consider the information, and the opportunity to question the Investigator or other independent parties to decide whether they will participate in the trial. Electronic informed consent will be obtained prior to completing the two screening questionnaires. Written informed consent will be obtained at the first meeting with the participant, which will be scheduled within one week of completing the screening questionnaires. Written informed consent will include participant dated signature and dated signature of the person who presented and obtained the informed consent. The person who obtained the consent must be suitably qualified and

experienced, and have been authorised to do so by the Chief/Principal Investigator. The original signed form will be retained at the trial site.

#### 8.4 Randomisation

Random allocation to the three trial conditions (iCT, Mind-Online, standard practice) will be at a 1:1:1 ratio, stratified by site and initial eligibility (above or below cut-off on PHQ-9 and PCL-5 at screening) by the Oxford Clinical Trials Research Unit (OCTRU).

#### 8.5 Subsequent Assessments

Participants will complete assessments with an independent trained assessor who will be unaware of trial condition at baseline, 6, 52 and 104 weeks. They will also complete questionnaires on these occasions.

#### 8.6 Discontinuation/Withdrawal of Participants from Trial Treatment

Each participant has the right to withdraw from the trial at any time. The reason for withdrawal will be recorded.

#### 8.7 Definition of End of Trial

The end of trial is the date of the last follow up with the last participant.

### 9. INTERVENTIONS

Internet-delivered cognitive training for resilience (iCT-R) and Mind-Online will be delivered over 6 weeks, with the support of the trained research assistant (wellbeing coach) by email, SMS and phone calls (on average taking up to 1 hour of research assistant time for both treatments). Participants will be able to print the modules they complete. The research assistant will send top up reminders every month and every 6 months, participants will have the opportunity to talk with the research assistant about putting their tools in place or accessing and practising the wellbeing information they have learned.

#### 9.1 Internet-delivered cognitive training for resilience (iCT-R)

iCT-R follows a similar format to the internet-based programmes we have developed for social anxiety and PTSD. The core information is delivered in modules of which there are six. The modules include whiteboard videos to explain concepts, audio files for practicing concrete thinking, testimony from qualified paramedics and video footage of student paramedic call-outs for use in the modules' experiential exercises. The modules are as follows:

- It Matters What You Focus On: Helpful and Unhelpful Attention
- Get Out of Your Head: Helpful and Unhelpful Thinking
- Habits and Dwelling: How to Change Them
- Dealing with Unwanted Memories: Then vs Now
- Dealing with Worry
- My Blueprint

#### 9.2 Mind-Online

The alternative resilience programme is Mind Online, a series of six modules available online covering information and advice about wellbeing and mental health topics, which have demonstrated high acceptability to emergency workers in a previous trial (4). The six modules are:

- Dealing with Stress
- Sleep Problems
- Anger
- Depression
- Post-traumatic Stress Disorder
- Mindfulness

Participants will receive the same frequency, type and duration of remote support as in iCT-R.

### 9.3 Treatment fidelity

Treatment fidelity will be assessed by an independent rater. The content of a random sample of email communications will be scored for reference to content relevant to each training programme.

### 9.4 Standard Practice

Participants initially allocated to the standard practice will be offered iCT-R at 104 weeks.

## 10. SAFETY REPORTING

### 10.1 Definitions

| Term                               | Definition                                                                                                                                                                                                                                                                                                                                                                                             |
|------------------------------------|--------------------------------------------------------------------------------------------------------------------------------------------------------------------------------------------------------------------------------------------------------------------------------------------------------------------------------------------------------------------------------------------------------|
| Adverse Event (AE)          | Any untoward medical occurrence in a participant or clinical trial participant and which are not necessarily caused by or related to that product                                                                                                                                                                                                                                                      |
| Serious Adverse Event (SAE) | Any adverse event that - 
 
• Results in death
 
• Is life-threatening*
 
• Required hospitalisation or prolongation of existing hospitalisation**
 
• Results in persistent or significant disability or incapacity
 
• Consists of a congenital anomaly or birth defect
 
• Other medically important condition***
 
 |

**\*Note:** The term 'life-threatening' in the definition of serious refers to an event in which the trial participant was at risk of death at the time of the event or it is suspected that use or continued use of the product would result in the subject's death; it does not refer to an event which hypothetically might have caused death if it were more severe.

## 10.2 Causality

The Principal Investigator will assess each SAE to determine the causal relationship:

| Relationship     | Description                                                                                                                                                                                                                                                                                                                   | Reasonable possibility that the SAE may have been caused by the intervention? |
|------------------|-------------------------------------------------------------------------------------------------------------------------------------------------------------------------------------------------------------------------------------------------------------------------------------------------------------------------------|-------------------------------------------------------------------------------|
| Unrelated | There is no evidence of any causal relationship with the trial/intervention                                                                                                                                                                                                                                                   | No                                                                            |
| Unlikely  | There is little evidence to suggest there is a causal relationship with the trial/intervention (e.g. the event did not occur within a reasonable time after the intervention). There is another reasonable explanation for the event (e.g. the participant's clinical condition, other concomitant treatment).                | No                                                                            |
| Possible  | There is some evidence to suggest a causal relationship with the trial/intervention (e.g. because the event occurs within a reasonable time after the intervention). However, the influence of other factors may have contributed to the event (e.g. participant's physical health or exposure to critical incident at work). | Yes                                                                           |
| Probable  | There is evidence to suggest a causal relationship and the influence of other factors is unlikely.                                                                                                                                                                                                                            | Yes                                                                           |
| Definite  | There is clear evidence to suggest a causal relationship and other possible contributing factors can be ruled out.                                                                                                                                                                                                            | Yes                                                                           |

## 10.3. Expectedness

The Chief Investigator will assess each SAE to perform the assessment of expectedness. The expectedness assessment should be made according to the information as detailed in the protocol.

### Reference Safety Information (RSI)

There are no expected side effects linked to either intervention.

Expectedness decisions must not take into account factors such as the participant population and participant history. Expectedness is not related to what is an anticipated event within a particular disease. SAEs which add significant information on specificity or severity of a known, already documented adverse event constitute unexpected events.

## 10.4 Procedures for Recording Adverse Events

All AEs occurring during the trial that are observed by the research team or reported by the participant, will be recorded. The following information will be recorded: description, date of onset and end date, severity, assessment of relatedness to intervention, and action taken. Follow-up information should be provided as necessary. The severity of events will be assessed on the following scale: 1 = mild, 2 = moderate, 3 = severe.

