## 10.6 Monitoring for negative effects of treatment delivery over the internet

We will assess participant's evaluation of the internet modules and design through a feedback and rating form at the end of each module and in comments to the research assistant in emails or telephone calls.

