## **STUDY METHODS**

### **Trial Design/framework**

#### **Interventions:**

The study is a single-blind (assessors blind) randomised controlled trial. There are three arms: iCT-R, Mind-Online, and Standard Practice. The newly developed intervention iCT-R aims to modify rumination and appraisals linked to low resilience and risk for PTSD and MDD with a six-session supported online intervention. A trained research assistant provides email feedback on students' responses and, through an automated SMS programme, sends regular reminders of key points of the intervention and notifications to practice the skills. The other intervention also contains six online modules and includes information and advice about stress, sleep problems, anger, depression, PTSD, and mindfulness. Participants will receive the same frequency, type and duration of online support as in iCT-R. The third

arm is Standard Practice. Participants have access to the usual support offered through their university, but they will not receive any online modules or online support.

Time points:

Data are collected pre-intervention, post-intervention, at 6-months follow-up, at 1-year follow-up and at 2-years follow-up.

More information on the intervention arms and measurement time points can be found in the published trial protocol ([name] et al., 2018).

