## **Harms**

No adverse events are anticipated. The procedure for adverse events (AE) and serious adverse events (SAE) are reported in the trial protocol paper.

[name], [name], [name], [name], [name], [name], [name], [name], [name], [name], [name], & [name] Cognitive resilience training to prevent PTSD and MDD in paramedics: A randomised controlled trial.

The total number of serious adverse events (SAE) and the number of SAE per participant (if at least one SAE) are reported in each randomised intervention group. If there is at least one SAE, a comparison between the intervention groups regarding the total number of SAE and the number of SAE per participant is made. The safety analysis is also ITT. Results of these comparisons, such as statistical tests and ratios, are reported.

No additional safety analyses are needed due to the Covid pandemic as the continuation of the trial during the pandemic did not put participants at a higher risk.

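### SAE comparisons with Standard Practice are open to ascertainment bias, because events are recorded as observed or reported and only the training arms have coach contact and module feedback

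*Combined protocol and SAP*

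**What the plan says.** **Capture.** Protocol section 10.4 sets one rule for all arms: "All AEs occurring during the trial that are observed by the research team or reported by the participant, will be recorded". Section 10.5 covers onward reporting once the investigator knows of an SAE, not how SAEs are found. Appendix B lists interviews, questionnaires, samples and a compliance measure, but no adverse-event item.

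**Contact in the training arms.** Both online programmes run for six weeks "with the support of the trained research assistant (wellbeing coach) by email, SMS and phone calls", taking on average up to one hour of staff time. Section 9 adds: "The research assistant will send top up reminders every month and every 6 months, participants will have the opportunity to talk with the research assistant". Section 9.2 matches the two programmes: "Participants will receive the same frequency, type and duration of remote support as in iCT-R". Section 10.6, on negative effects of internet delivery, relies on a "feedback and rating form at the end of each module and in comments to the research assistant in emails or telephone calls".

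**Contact in Standard Practice.** Under SAP Trial Design/framework, participants keep the usual university support, but "they will not receive any online modules or online support".

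**Analysis.** SAP Harms says that, once any such event has occurred, "a comparison between the intervention groups regarding the total number of SAE and the number of SAE per participant is made". Tests and ratios are to be reported on an intent-to-treat basis. No common detection window, caveat or sensitivity analysis for unequal ascertainment is given.

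**The concern.** A comparison of recorded SAEs estimates the ratio of true risks multiplied by the ratio of detection probabilities. The second factor is 1 only if an event is equally likely to reach the trial team whichever arm the participant is in. Here detection rests on observation or report, and two of the three arms have extra routes for both. The expected direction is more complete recording in the training arms. That could look like harm from training, or could hide a real reduction in SAEs.

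The stake is moderate. There are no stopping rules (protocol 11.4) and no Data Monitoring Committee (SAP, Statistical Interim Analysis), so the Harms section holds the main planned quantitative safety analysis. SAP Timing of Final Analysis also contemplates early roll-out of iCT-R if it does better than Mind-Online or Standard Practice, so readers will want a harms comparison they can trust.

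**Working it through.** **1. Figures the plan supplies.** It gives no SAE rate, capture rate or safety power. The only input borrowed from it is arm size, and that reproduces. With risks 0.25 and 0.125 (mean 0.1875), two-sided α = 0.05 and 80% power:

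n = [1.96·√(2 × 0.1875 × 0.8125) + 0.8416·√(0.25 × 0.75 + 0.125 × 0.875)]² / 0.125² = 152 per arm.

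Then 2 × 152 = 304, 3 × 152 = 456, 456/0.80 = 570, and 570/3 = 190 randomised per arm.

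**2. Routes by which an SAE can reach the team after baseline.**

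| Route | iCT-R | Mind-Online | Standard Practice | Source |
|---|---|---|---|---|
| Blinded interview at 6, 52, 104 weeks (PTSD and MD modules) | yes | yes | yes | Protocol 8.5, App. B |
| Questionnaires at 6, 24, 52, 104 weeks, no AE item listed | yes | yes | yes | App. B |
| Cortisol and CRP samples at 6, 52, 104 weeks | yes | yes | yes | App. B |
| Coach by email, SMS and phone during training | yes | yes | no | Protocol 9 |
| Six-monthly chance to talk | yes | yes | no | Protocol 9 |
| Monthly reminders | yes | yes | no | Protocol 9 |
| Module feedback and comments | yes | yes | no | Protocol 10.6 |

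The SAP (Randomisation and Blinding) says online questionnaires are completed without the researchers' involvement. For Standard Practice, Appendix B schedules no assessment between 52 and 104 weeks.

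**3. Illustration; every rate here is an assumption.** Recorded risk = true risk × capture. With equal true risk, the apparent ratio is the capture ratio: 0.90/0.75 = 1.20, 0.90/0.60 = 1.50, 0.90/0.45 = 2.00. Expected recorded events per arm are 190 × true risk × capture.

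The pairwise column is the chance that a two-sided 5% test shows a significant excess in one training arm (nominally 2.5%): Φ[(d − 1.96·SE₀)/SE₁], where d is the difference in recorded risk and SE₀ and SE₁ are its pooled and unpooled standard errors. For 5% risk and 60% capture: d = 0.045 − 0.030 = 0.015, SE₀ = 0.01949, SE₁ = 0.01948, giving Φ(−1.19) = 11.7%. The last column is a simulated three-arm chi-square (20,000 runs), which rejects in 4.6% to 4.8% of runs when capture is 90% in all arms.

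| True SAE risk | Capture, training / Standard Practice | Recorded events per 190 | Apparent ratio | Pairwise false excess | Three-arm rejection |
|---|---|---|---|---|---|
| 2% | 90% / 75% | 3.4 v 2.9 | 1.20 | 4.2% | 4.9% |
| 2% | 90% / 60% | 3.4 v 2.3 | 1.50 | 7.0% | 6.3% |
| 2% | 90% / 45% | 3.4 v 1.7 | 2.00 | 11.5% | 8.5% |
| 5% | 90% / 75% | 8.6 v 7.1 | 1.20 | 5.6% | 6.3% |
| 5% | 90% / 60% | 8.6 v 5.7 | 1.50 | 11.7% | 10.5% |
| 5% | 90% / 45% | 8.6 v 4.3 | 2.00 | 22.8% | 19.6% |
| 10% | 90% / 75% | 17.1 v 14.3 | 1.20 | 7.6% | 7.8% |
| 10% | 90% / 60% | 17.1 v 11.4 | 1.50 | 19.7% | 17.8% |
| 10% | 90% / 45% | 17.1 v 8.6 | 2.00 | 41.6% | 40.2% |

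The normal approximation is rough at the smallest counts. Masking works the same way: with a capture ratio of 1.50, a true ratio of 0.67 would appear as 0.67 × 1.50 = 1.00. For iCT-R versus Mind-Online, equal capture gives 1.00 under equal true risk.

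**The case against.** The case on the other side has real force.

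- **Report may include being asked.** A reader might infer that events count only if volunteered. Section 10.4 does not say so: a reported event may have been prompted, and Appendix B may list only formal instruments. The SAP refers AE procedures to the published protocol paper, which may say more. What stands is that no standard enquiry appears in these documents.
- **The contact gap is easy to overstate.** A reader might count about 24 reminders and 4 talks over two years. Section 9 gives no end date for either, and the SAP describes reminders sent by an automated SMS programme. An outgoing text is a weak chance to learn of an SAE. The clearly two-way contact is the coach support and the optional talks.
- **SAEs are hard to miss.** The SAP tests only SAEs, and all arms share blinded interviews and sampling. This makes very low capture less plausible, and nothing in the documents supports 45% or 60%. With 75% capture and 5% risk, three-arm rejection is 6.3%, close to nominal.
- **The priority contrast is sheltered.** The SAP ranks iCT-R versus Mind-Online first, and support there is matched.
- **Restricting the test has its own cost.** It is tempting to test only events found at common assessments. That would drop known deaths and events in participants lost to follow-up (20% attrition is allowed for), against the SAP's intent-to-treat safety analysis.

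These points limit the size and shape of the problem. They do not make detection independent of arm for Standard Practice.

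**Conclusion.** The SAE comparison with Standard Practice, and any three-arm SAE test, is open to ascertainment bias. The likely direction is relative over-recording in the training arms. The stronger statement, that the comparison is biased or will show false harm, is not supported: no capture or SAE rates are given, so the ratios and error rates above only show sensitivity to assumed values. The conclusion rests on two readings: that no common AE enquiry exists beyond what the documents list, and that coach contact and module feedback raise the chance of an event becoming known. iCT-R versus Mind-Online is largely unaffected. The efficacy sample size is not touched. This is an inexpensive improvement to the safety analysis and does not threaten the trial's main conclusion.

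**What to change.** **Protocol 10.4.** Add one AE/SAE question, worded identically for all three arms, to the questionnaires or blinded interviews already scheduled at 6, 24, 52 and 104 weeks. The SAP version is dated 21 April 2021 and already reports 1-year rates, so in practice this may reach only outstanding 2-year assessments.

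**SAP Harms.**
- Keep every known SAE, including deaths, in the intent-to-treat tabulation, and record how each was found: common assessment, coach contact or other.
- Make iCT-R versus Mind-Online the main SAE contrast.
- Present comparisons with Standard Practice descriptively, with the ascertainment limitation stated.
- Add a sensitivity analysis limited to events found through routes common to all arms, with deaths retained. Use admissions from the CSRI and TiC-P only if those forms record them. The documents do not describe their content or recall period, and Appendix B omits them at 24 weeks.

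**Cost.** One extra item, a short amendment to each document, and a less formal comparison with Standard Practice. No new visits are needed and N stays at 570. The SAP changes can be made even if data collection has finished.

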## 10.5 Reporting Procedures for Serious Adverse Events

All SAEs must be reported on the SAE reporting form to the REC within 15 working days of the Principal Investigator becoming aware of the event, using the Health Research Authority safety report form for a non-Clinical Trial of an Investigation of a Medicinal Product (non-CTIMP).

It will also be reviewed at the next Trial Steering Committee meeting. All SAE information must be recorded on an SAE form and faxed, or scanned and emailed, to the REC.

Additional and further requested information (follow-up or corrections to the original case) will be detailed on a new SAE Report Form and faxed/emailed to the REC.

